### 8.3 Analysis of secondary outcomes

The continuous outcomes of serum  $\beta$ -carotene and ascorbic acid levels will be compared between groups using difference in means with 95% confidence intervals, and t-tests will be used to derive two-sided  $p$ -values. Alternative non-parametric tests will be used if the data does not meet the assumptions of t-tests and these may include the Wilcoxon Rank Sum test.

The binary outcomes of self-reported financial security and food security status will be compared between groups using risk differences with 95% confidence intervals, and chi-squared tests to derive two-sided  $p$ -values.

The count outcomes of self-reported vegetable and fruit consumption, will be compared between groups using the Wilcoxon rank sum test, where a  $p$ -value of  $<0.05$  will be sufficient to reject the null hypothesis of no difference.

For the ordinal outcomes of self-reported health-status and food-security score ordinal regression will be used using odds ratios with 95% confidence intervals.

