## **Inclusion/Exclusion Criteria**

Participants will be adult (age >19 years) patients of the two participating primary care who have either “pre-diabetes” (A1c 6.0 to 6.4) or diabetes (A1c  $\geq$  6.5) based on bloodwork done in the last 3 months and who either score 2 or above on the six-item food insecurity instrument or who report trouble “making ends meet”. We will exclude people who live with a current study participant (to avoid contamination), people who are palliative (have a life expectancy < 6 months), people with multiple (>3) life-threatening allergies to common foods, people who require total parenteral nutrition, and people with a blood dyscrasia that interferes with hemoglobin A1c testing (anemia due to iron deficiency, B12 deficiency and folate deficiency). We will also exclude individuals with very poorly controlled diabetes (A1c > 11) as interventions other than food such as medicines may be the most important interventions. We will also exclude individuals with very poorly controlled diabetes (A1c > 11) as interventions other than food such as medicines may be the most important interventions.

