ask participants in the intervention group how often they accessed the food retailer, about their participation in educational and community building activities, about wasted food and about whether they would have wanted other foods to be provided.

We will perform a cost-effectiveness analysis from a societal perspective that considers direct and indirect costs of the intervention and direct and indirect effects including changes in healthcare utilization. We will assess the economic implications of the potential effects of the intervention including costs associated with primary care, emergency department use, and complications of diabetes based on previous studies of the association between hemoglobin A1c and health outcomes.

We will report demographic characteristics collected at the time of enrollment including age, sex, gender, education level, household income, income source, ethnicity, and medical comorbidities.

We will employ an intention to treat analysis. The primary analysis of the follow-up A1c (follow-up measurement) will be adjusted for baseline hemoglobin A1c and analysed using analysis of covariance (ANCOVA). Binary outcomes will be compared between groups using risk differences with 95% confidence intervals, and chi-squared tests to derive two-sided p-values. Continuous outcomes will be compared between groups using difference in means with 95% confidence intervals, and t-tests to derive two-sided p values. Count outcomes will be analysed using rate ratios from quasi-Poisson models with 95% confidence intervals and two-sided p-values, which will be adjusted for baseline values whenever available. Ordinal outcomes will be analyzed using ordinal regression.

Randomization will be stratified by site. We will report both the unadjusted analysis for the primary outcome and the analysis adjusted for age, sex, whether or not prescribed diabetes oral medicines at baseline, and whether or not prescribed insulin at baseline.

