### 5.3 Data preparation

The primary outcome of HbA1c at 6 months will be assessed via laboratory testing for study purposes or review of the electronic primary care record. This is a continuous variable. The primary outcome will be adjusted for HbA1c at baseline, which will be assessed via review of the electronic primary care record. This is a continuous variable.

Serum  $\beta$ -carotene and ascorbic acid levels at 6 months will be assessed via laboratory testing for study purposes.

Data on self-reported food security, self-reported financial security, and self-reported vegetable and fruit consumption will be collected through surveys administered online, over the phone, or in-person at 6 months. Baseline data on self-reported food security and baseline self-reported vegetable and fruit consumption were collected at through surveys conducted over the phone or in-person at the recruitment visit.

Self-reported health status will be measured on a 5-point likert scale, where participants were asked the standard question at follow-up "In general, how would you rate your health today?" Potential responses are: very good, good, moderate, bad, very bad and decline to respond.

Self-reported food security will be assessed using 6 standard and validated items adapted from the Canadian Community Health Survey (Household Food Security Survey Module), applied to the last 6 months (12). The instrument assesses worry about food running out due to financial constraints, food not lasting, and the inability to afford balanced meals using the following questions:

1. The food that you and other household members bought just didn't last, and there wasn't any money to get more. Was that often true, sometimes true, or never true in the past 6 months? Potential responses are: Often true, Sometimes true, Never true, Don't know/Refuse to answer
2. You and other household members couldn't afford to eat balanced meals. Was that often true, sometimes true, or never true in the past 6 months? Potential responses are: Often true, Sometimes true, Never true, Don't know/Refuse to answer
3. In the past 6 months, did you or other adults in your household ever cut the size of your meals or skip meals because there wasn't enough money for food? Potential responses are: Yes, No, Don't know/Refuse to answer

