  - a. (If answered Yes to question 3) How often did this happen? Potential responses are: Almost every month, Some months but not every month, Only 1 or 2 months, Don't know/Refuse to answer
4. In the past 6 months, did you (personally) ever eat less than you felt you should because there wasn't enough money to buy food

5. In the past 6 months, were you (personally) ever hungry but didn't eat because you couldn't afford enough food? Potential responses are: Yes, No, Don't know/Refuse to

Participants can answer affirmatively to 0 to 6 of the questions. We will assess food security status as a binary variable, where less than 2 affirmative responses indicates "food secure" and 2 or more affirmative responses indicates more "food insecure." This is based on Health Canada's approach to interpreting the data from the Household Food Security Survey Module (13). We will also examine food security as a raw score between 0 to 6 (based on the number of affirmatively answered questions) as a sensitivity analysis.

Self-reported financial security is a categorical variable where participants were asked the standard question at follow-up "Do you have trouble making ends meet at the end of the month?" Potential responses were: yes, no and decline to respond.

Self-reported vegetable consumption and self-reported fruit consumption are both categorical variables, measured at both baseline and 6 months. Participants were asked "How often to you eat vegetables?" and "How often do you eat fruits?" Potential responses included: 0 times per day, once per day, twice per day, three times per day, four times per day, five or more times per day, or decline to answer.

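### SAP 8.3 compares food security, one of seven secondary outcomes, without using the baseline food-security data that were collected, at an avoidable cost in precision

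*Combined protocol and SAP*

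**What the plan says.** - **Binary status.** SAP 8.3: "The binary outcomes of self-reported financial security and food security status will be compared between groups using risk differences with 95% confidence intervals", with "chi-squared tests to derive two-sided" p-values. No covariate is named. The protocol, under its secondary outcome measures, gives the same method for binary outcomes.
- **Score from 0 to 6.** SAP 8.3: "For the ordinal outcomes of self-reported health-status and food-security score ordinal regression will be used using odds ratios with 95% confidence intervals". No baseline term is named. SAP 5.3 labels the score a sensitivity analysis: "We will also examine food security as a raw score between 0 to 6".
- **Baseline data.** SAP 5.3: "Baseline data on self-reported food security and baseline self-reported vegetable and fruit consumption were collected" by survey at recruitment.
- **Entry.** The protocol's eligibility criteria take people "who either score 2 or above on the six-item food insecurity instrument or who report trouble" making ends meet. Someone scoring 0 or 1 can therefore enter by the second route.
- **Outcome cut-off.** SAP 5.3: "less than 2 affirmative responses indicates" food secure, and 2 or more food insecure. This is the same threshold as at entry.
- **Adjustment elsewhere.** The A1c analysis is adjusted for baseline A1c (protocol; SAP 5.3), and the covariates in SAP 8.2 belong to A1c alone. The protocol's phrase "which will be adjusted for baseline values whenever available" is attached to count outcomes only. Nothing in either document adds a baseline term for food security.

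**The concern.** The entry rule allows two kinds of participant with different prospects on this outcome. Those who start food insecure can improve or stay as they are; those who start food secure can only stay as they are or worsen. Where a person starts is likely to predict where that person ends. An analysis that pools the two groups counts the difference between them as noise, although the variable that separates them was collected.

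Randomisation is not stratified by food security, so the arms may by chance differ in their mix of entrants. A crude comparison carries that difference into the estimate. Secondary hypothesis 5 is a superiority hypothesis on food security, the sample size was set for A1c, and no power is stated for food security. There is thus no reason to give away precision that the existing data could supply.

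**Working it through.** **1. The plan's own figure.** The documents state no power or precision for food security, so I take the number per arm from the A1c calculation in SAP 7 (difference 0.4, SD 1.3, two-sided alpha 0.05, power 80%):

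n per arm = 2 × (1.960 + 0.842)² × 1.3² / 0.4² = 165.8, so 166 per arm and 332 in total, as stated. With 15% dropout, 332 / 0.85 = 390.6, against 390 stated. I use 166 evaluable per arm below.

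**2. Formula.** Let q be the share food insecure at entry, a the probability of being insecure at six months if insecure at entry, and b the same probability if secure at entry. All three are assumptions. Using common rates in both arms:

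- p = q·a + (1 − q)·b
- crude variance per person: p(1 − p)
- variance within baseline strata: q·a(1 − a) + (1 − q)·b(1 − b)
- reduction = 1 − within / crude, which equals phi², the squared correlation between baseline and follow-up status.

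**3. Results with 166 per arm.** The half-width is 1.96 × √(2 × variance / 166), in percentage points. The power column shows what a crude test with 80% power would become.

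| q | a | b | Crude variance | Within-stratum variance | Reduction | 95% CI half-width | Power from 80% |
|---|---|---|---|---|---|---|---|
| 0.50 | 0.8 | 0.2 | 0.2500 | 0.1600 | 36% | 10.8 → 8.6 | 93.8% |
| 0.70 | 0.8 | 0.3 | 0.2275 | 0.1750 | 23% | 10.3 → 9.0 | 89.1% |
| 0.80 | 0.6 | 0.3 | 0.2484 | 0.2340 | 5.8% | 10.7 → 10.4 | 82.3% |
| 0.95 | 0.8 | 0.2 | 0.1771 | 0.1600 | 9.7% | 9.1 → 8.6 | 83.8% |
| 0.95 | 0.6 | 0.3 | 0.2428 | 0.2385 | 1.8% | 10.6 → 10.5 | 80.7% |

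The second row is worth 332 / (0.1750 / 0.2275) = about 432 evaluable participants instead of 332. The first and last rows are the extremes of the assumed range.

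**4. Chance imbalance is the same quantity seen from another side.** In the second row, the baseline insecure share differs between arms with standard deviation √(2 × 0.7 × 0.3 / 166) = 5.0 points. Each such difference moves the crude risk difference by (0.8 − 0.3) × 5.0 = 2.5 points. The variance removed by stratifying is 2 × (0.2275 − 0.1750) / 166 = 0.00063, whose square root is also 2.5 points. Precision and imbalance should not be counted as two separate losses.

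**5. Ordinal score.** A simulation (166 per arm, about 25% scoring 0-1 at baseline, latent shift of 0.3 SD, 300 replicates per setting, Monte Carlo error about 3 points) compared ordinal regression without and with the baseline score. Power went from 78% to 78% at latent correlation 0.3, from 72% to 86% at 0.5, and from 76% to 92% at 0.7. With no effect and correlation 0.5, rejection rates for the crude and adjusted analyses, binary and ordinal, lay between 4% and 6%. At correlation 0.5 the mean log odds ratio was −0.50 without and −0.58 with the baseline score, because the adjusted odds ratio is conditional.

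**The case against.** The strongest reply is that nothing here is an error. A crude risk difference with a chi-squared test is valid in a randomised trial, its confidence interval already allows for chance imbalance, and the SAP follows the protocol's method for binary outcomes. Food-secure entrants can worsen, so they still inform the comparison. All of this stands, and it makes the point an improvement in efficiency.

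The gain may also be small. A score of 2 or more is itself an entry route, so most participants may be food insecure at entry; at 95% the reduction is 1.8% to 9.7% under the rates above. SAP 5.3 gives no recall period for the baseline instrument. The follow-up items cover six months, while the protocol describes three food-security questions, the first over 30 days. A mismatch in recall would lower the correlation and with it the gain. This stands too, but it is no reason against using the covariate.

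A reader might infer more than the documents support:

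- **That food security is a central outcome.** It is fifth of seven unranked secondary hypotheses, and SAP 5.3 calls the 0-6 score a sensitivity analysis.
- **That financial security needs the same adjustment.** SAP 5.3 does not list a baseline measure of it and describes the question as asked at follow-up. Someone who qualified on the food score need not have been asked it at entry.
- **That condition must be added as the randomisation stratum.** The protocol's design section and SAP 2.2 name condition, but the protocol's analysis text says site. Nothing in the documents suggests that condition predicts food security.

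**Conclusion.** The omission is clear: SAP 8.3 states no baseline term for food security, although the baseline was collected and the entry rule spans the outcome cut-off. The consequence is a wider confidence interval than the data may require. It is not bias, and the type I error is not at risk.

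The size cannot be fixed from the documents, which give no baseline mix and no persistence rates. Under the assumed ranges (50-95% insecure at entry, 60-80% of those still insecure at six months, 20-30% of food-secure entrants newly insecure) the variance reduction runs from about 2% to 36%. The lower end applies if nearly everyone enters food insecure. The change is worth making because it uses data already held and keeps the risk-difference scale, but the plan is not invalid without it.

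**What to change.** In SAP 8.3:

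1. Estimate the food-security risk difference, with its 95% confidence interval and p-value, stratified by baseline food-security status (for example Mantel-Haenszel) or standardised over it from a logistic model.
2. Add the baseline score to the ordinal regression for the 0-6 score, and state that the odds ratio is then conditional on it.
3. Give missing or refused baseline answers their own stratum, or impute them, and say which.
4. Keep the crude comparison as a supporting result.
5. Add the randomisation stratum only after the statements naming condition (protocol design section, SAP 2.2) and site (protocol analysis text) have been reconciled.
6. Leave financial security unadjusted, since a baseline for all participants is not documented.

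The cost is SAP wording and a few lines of code, with no new data. The one downside is procedural. The change departs from the protocol's method for binary outcomes, and SAP 7 already reports all 390 participants recruited. It should therefore be dated and justified. The documents do not say whether outcome data have been seen; if they have, the adjusted result should be reported beside the crude one and labelled post hoc.

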### *Secondary outcome measures*

Secondary outcomes will include self-reported health, self-reported food-security, self-reported financial security, carotenoid level, and self-reported fruit and vegetable consumption. Carotenoid levels will be measured during a visit at the end of the study (months 5 or 6). Serum levels of  $\alpha$ -carotene,  $\beta$ -carotene, lutein,  $\beta$ -cryptoxanthin, and ascorbic acid correlate with self-reported vegetable and fruit consumption although the absolute value varies based on characteristics of the individual such as age and body mass index. It is thus an appropriate measure to use as a trial outcome. Self-reported health status is associated with mortality and is based on both current health and perceived health risks. The standard question is: "In general, how would you rate your health today?" Potential responses are: very good, good, moderate, bad, very bad and decline to respond. Self-reported food security will be assessed with three standard questions: "In the past 30 days, have you been concerned about having enough food for you or your family?" Potential responses are: yes, no and decline to respond. "Food you and other household members bought didn't last and there wasn't any money to get more?" Potential responses are: yes, no and decline to respond. Self-reported food security (balance): "You and other household members couldn't afford to eat balanced meals?" Potential responses are: yes, no and decline to respond. Self-reported vegetable consumption will be assessed using the standards question "How often to you eat vegetables?" Potential responses include: 0 times per day, once per day, twice per day, three times per day, four times per day, five or more times per day, or decline to answer. The same question will be applied to fruit consumption. Self-reported financial security will be assessed using the standard question "Do you have trouble making ends meet at the end of the month?"(44) Potential responses are: yes, no and decline to respond. We will ask about trade-offs between food and diabetes supplies, that is, whether participants put off purchasing food to buy diabetes supplies or vice versa (never, sometimes, often, regularly). We will track changes in medicines including changes in dose based on information available in the electronic health records. We will also

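### SAP 8.3 compares fruit and vegetable intake by an unadjusted Wilcoxon test with no effect estimate, although baseline intake is collected and the protocol specified baseline-adjusted estimates with confidence intervals

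*Combined protocol and SAP*

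**What the plan says.** **Fruit and vegetable intake.** The protocol, in the analysis paragraphs that follow its secondary outcomes, states: "Count outcomes will be analysed using rate ratios from quasi-Poisson models with 95% confidence intervals and two-sided p-values". The sentence continues "which will be adjusted for baseline values whenever available". SAP 8.3 replaces this: "The count outcomes of self-reported vegetable and fruit consumption, will be compared between groups using the Wilcoxon rank sum test". The only further detail there is a 0.05 threshold for the p-value. The summary of changes lists an added site, a corrected sample size and the removal of the purchase restriction. It does not mention this switch.

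**Availability of baseline.** SAP 5.3 states: "Baseline data on self-reported food security and baseline self-reported vegetable and fruit consumption were collected". It repeats for the two intake items that they are measured at both time points.

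**Type of variable.** SAP 5.3 calls the intake items categorical. SAP 6.3 and 8.3 call them counts. The responses run from zero to a top category of five or more times per day.

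**Food security.** For binary outcomes the protocol says: "Binary outcomes will be compared between groups using risk differences with 95% confidence intervals, and chi-squared tests to derive two-sided p-values". SAP 8.3 agrees: "The binary outcomes of self-reported financial security and food security status will be compared between groups using risk differences with 95% confidence intervals". SAP 8.3 also applies ordinal regression to the 0–6 score, with odds ratios and 95% confidence intervals, and names no covariate.

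**The concern.** Intake and food security are the outcomes that would help explain the HbA1c result, whether positive or null. A reader will want to know by how much intake changed and how precisely that is known. A rank-sum p-value answers neither question. It is also the only analysis in SAP 8.3 without a planned estimate: the other outcomes get a mean difference, a risk difference or an odds ratio, each with an interval.

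Habitual intake and food security tend to persist within a person, so the baseline answer should explain part of the variation at follow-up. Leaving it out widens the uncertainty at no saving, because the data are already in hand. For intake, the SAP also departs from the protocol's method without giving a reason.

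**Working it through.** **1. The plan's own figure.** No power is stated for any secondary outcome. The only sample-size figure concerns HbA1c (SAP 7: difference 0.4 points, SD 1.3, alpha 0.05, power 80%). A two-sided normal-approximation calculation gives 166 per arm, 332 in total, as stated. Inflating for 15% loss gives 332 / 0.85 = 391, against 390 stated. I use 332 evaluable participants below only as the working sample size.

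**2. Protocol and SAP side by side.**

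| Outcome | Baseline collected? | Protocol | SAP 8.3 |
|---|---|---|---|
| Fruit, vegetables | Yes | Quasi-Poisson rate ratio, 95% CI, baseline-adjusted | Wilcoxon, p-value only |
| Food security, binary | Yes | Risk difference, chi-squared, unadjusted | Same |
| Food security, 0–6 score | Yes | Ordinal regression, no covariate named | Ordinal regression, no covariate named |
| Financial security | Eligibility question only | Risk difference, chi-squared, unadjusted | Same |

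Only the first row is a departure from the protocol.

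**3. Precision, linear approximation.** Adjusting for a baseline value with correlation r multiplies the variance of the group comparison by 1 − r². The documents do not give r, so a range is shown.

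| r | Variance removed | SE multiplied by | 332 participants worth |
|---|---|---|---|
| 0.3 | 9% | 0.954 | 332 / 0.91 = 365 |
| 0.5 | 25% | 0.866 | 332 / 0.75 = 443 |
| 0.7 | 49% | 0.714 | 332 / 0.51 = 651 |

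**4. Power for intake, by simulation.** Assumptions: six ordered levels with assumed cut-points, 332 participants, latent shift 0.25 SD. The comparison is Wilcoxon against a baseline-adjusted rank analysis.

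| r | Wilcoxon | Baseline-adjusted | Gain (points) |
|---|---|---|---|
| 0.2 | 58% | 59% | 1 |
| 0.3 | 57% | 60–61% | 3–4 |
| 0.5 | 60% | 69% | 9 |
| 0.7 | 58% | 80% | 22 |

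The range at r = 0.3 reflects two separate runs. Type I error was about 5% for both methods. In a small check, proportional-odds regression performed close to the adjusted rank analysis.

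Hand check on the ungrouped scale: the SE of the difference is √(2/166) = 0.110 SD, so 0.25 SD is 2.28 standard errors and power is Φ(2.28 − 1.96) = 62%. At r = 0.5 it becomes 2.28 / 0.866 = 2.63 standard errors and 75% power. At r = 0.7 it becomes 2.28 / 0.714 = 3.19 and 89%. The simulated powers lie somewhat below these, as expected once intake is grouped into six levels.

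**5. The protocol's own model.** A second simulation used counts capped at 5, a control mean of about 1.8 per day before capping and a rate ratio of 1.2, all assumed. Wilcoxon against baseline-adjusted quasi-Poisson gave 45% vs 49% (r about 0.23), 36% vs 43% (0.39) and 24% vs 30% (0.56). The gain is about 4 to 7 points.

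**6. Food-security status.** Under two assumed scenarios with a true 10-point risk difference, the unadjusted and adjusted standard errors were 0.0538 vs 0.0462 and 0.0546 vs 0.0396. The variance ratios are about 1.35 and 1.90. As shares of the unadjusted variance, adjustment removes 1 − 1/1.35 = 26% and 1 − 1/1.90 = 47%, which imply correlations of √0.26 = 0.51 and √0.47 = 0.69. Other scenarios, with 70–85% food insecure at baseline, gave excess variance of only 2–45%, which is 2–31% of the unadjusted variance. The gain therefore ranges from negligible to substantial, depending on how persistent food insecurity is.

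**The case against.** The strongest defence is that nothing here is invalid. Randomization makes the unadjusted comparisons unbiased, type I error is held, these are secondary outcomes, and no power target was set for them. All of that stands. It limits the point to precision and reporting.

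A second defence is that a rank test suits an ordered, top-coded scale better than the protocol's count model. That has force. It argues against simply reinstating quasi-Poisson, but it does not justify dropping the baseline value and the effect estimate. Ordinal regression keeps the advantage and supplies both, and SAP 8.3 already uses it elsewhere.

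A third is that the gain rests on an unknown correlation. This also stands: at r = 0.2 to 0.3 the power gain is slight. The missing effect estimate does not depend on r.

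Several stronger readings are tempting and should not be drawn:

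- *The protocol promised adjustment for food and financial security.* It did not. The baseline clause sits in the sentence on counts, and the protocol's and SAP's sentences on binary outcomes agree.
- *A baseline value of financial security is being ignored.* SAP 5.3 places that question at follow-up and does not list it among the baseline data. It otherwise appears only as one half of an either/or entry criterion, so its variation at entry is restricted.
- *The serum markers have the same defect.* The documents describe no baseline sample for them. The protocol says of their correlation with intake "although the absolute value varies based on characteristics of the individual such as age and body mass index", which makes age adjustment an option but not a requirement; a log-scale model would be a preference. The SAP's sentence "Alternative non-parametric tests will be used if the data does not meet the assumptions of t-tests" raises a separate, minor question of prespecification.
- *The method was changed in view of the results.* The documents show an unexplained switch and say nothing about its motive.

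**Conclusion.** The point holds for fruit and vegetable intake. The SAP departs from the protocol without explanation, leaves unused a baseline value that it says was collected, and plans no effect estimate or interval. For food security, the unused baseline is a missed gain in precision and not a departure. Bias is not at issue.

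For intake, the power forgone is about 1 to 4 points at r = 0.2–0.3, about 9 at r = 0.5 and about 22 at r = 0.7. These figures assume 332 evaluable participants, a 0.25 SD shift and chosen category cut-points, none of which the documents give for this outcome. The larger gains require strong persistence of intake over six months. The departure and the missing effect size follow from the text alone. The change is worth making because it uses data already in hand.

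**What to change.** In SAP 8.3:

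- **Fruit and vegetable intake.** Analyse each by proportional-odds regression on arm, with the baseline value of the same item and the randomization strata as covariates. Report the odds ratio with its 95% confidence interval and two-sided p-value. Record this as a change from the protocol's quasi-Poisson model, giving the ordered, top-coded responses as the reason, and describe the items as ordinal throughout SAP 5.3, 6.3 and 8.3.
- **Food-security score.** Add the baseline 0–6 score as a covariate to the planned ordinal regression.
- **Binary food-security status.** Report a baseline-adjusted, standardized risk difference with its 95% confidence interval. The baseline score is the better covariate here, because the eligibility rule restricts variation in the baseline binary status.
- **Strata.** State which they are. The protocol's design section and SAP 2.2 give condition, while the protocol's analysis text gives site.

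No new data are needed. The cost is slightly more analysis work and reliance on a proportional-odds assumption, which should be checked and reported. Declined or missing baseline answers need a stated rule; SAP 8.2 already allows for multiple imputation of missing baseline characteristics. No change is needed to the financial-security analysis on this ground.
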